## Abstract

**Background:**

Time in therapeutic range (TTR) is a measurement of quality of warfarin therapy and lower TTR values (<50%) are associated with greater risk of thromboembolic and bleeding events. Recently, we developed a pharmacogenetic-based warfarin dosing algorithm specifically calibrated for a Brazilian patient sample. The aims of this study are: to evaluate the impact of a genetic-based algorithm, compared to traditional anticoagulation, in the time to achieve the therapeutic target and in TTR percentage; and to assess the cost-effectiveness of genotype-guided warfarin dosing in a specific cohort of patients with low TTR (<50%) from a tertiary cardiovascular hospital.

**Methods/design:**

This study is a randomized controlled trial in patients (*n* = 300) with atrial fibrillation with TTR < 50%, based on the last three INR values. At the first consultation, patients will be randomized into two groups: TA group (traditional anticoagulation) and PA group (pharmacogenetic anticoagulation). For the first group, the physician will adjust the dose according to current INR value and, for the second group, a pharmacogenetic algorithm will be used. At the second, third, fourth and fifth consultations (with an interval of 7 days each) INR will be measured and, if necessary, the dose will be adjusted based on guidelines. Afterwards, patients who are INR stable will begin measuring their INR in 30 day intervals; if the patient’s INR is not stable, the patient will return in 7 days for a new measurement of the INR. Outcomes measures will include the time to achieve the therapeutic target and the percentage of TTR at 4 and 12 weeks. In addition, as a secondary end-point, pharmacoeconomic analysis will be carried out. Ethical approval was granted by the Ethics Committee for Medical Research on Human Beings of the Clinical Hospital of the University of São Paulo Medical School.

**Discussion:**

This randomized study will include patients with low TTR and it will evaluate whether a population-specific genetic algorithm might be more effective than traditional anticoagulation for a selected group of poorly anticoagulated patients.

**Trial registration:**

ClinicalTrials.gov, NCT02592980. Registered on 29 October 2015.

## Background

Warfarin is a vitamin K antagonist and is the most widely prescribed oral anticoagulant agent worldwide [1]. It is used to prevent morbidity and mortality due to thromboembolism and, for this reason, it is very important to achieve an optimal anticoagulant therapy [2]. Furthermore, warfarin has a narrow therapeutic range and, consequently, patients usually have difficultly achieving and maintaining the therapeutic target [3–5].

Time in therapeutic range (TTR) is a measure of the quality of warfarin therapy, i.e., the percentage of time a patient’s INR (international normalized ratio) is within the desired treatment target. Lower TTR values (<50%) are associated with greater risk of thromboembolic and bleeding events; while higher TTR values (>65%) are associated with therapeutic benefits [6, 7]. Some studies identified factors that can affect TTR, such as the use of age, gender, race, and concomitant medications for predicting one’s ideal dosage [8–15]. In this scenario, some studies have assessed the impact of pharmacogenetic algorithms to guide the beginning of treatment. Pirmohamed et. al followed-up, for 12 weeks, patients who were recruited in the United Kingdom and Sweden. They used a slightly modified version of the International Warfarin Pharmacogenetics Consortium algorithm for predicting maintenance doses. They identified that the mean percentage of TTR was higher in the genotype-guided group (67.4%) compared with the control group (60.3%, *p* < 0.001) [16]. Verhoef et al studied patients taking acenocoumarol or phenprocoumon recruited in the Netherlands and Greece. They used an algorithm developed by EU-PACT group for phenprocoumon and acenocoumarol drugs [17]. They identified that genotype-guided dosing did not improve the TTR during the first 12 weeks after the initiation of therapy (61.6 and 60.2%, *p* = 0.52). However, they identified different TTR during the first 4 weeks after the initiation of treatment comparing pharmacogenetic and control groups (52.8 and 47.5%, *p* = 0.02) [18]. Kimmel et al, studied patients from 18 clinical centers in the United States. They used an algorithm developed by the COAG group [19]. The authors concluded that genotype-guided dosing of warfarin did not improve anticoagulation control during the first 4 weeks of therapy [20].

Recently, we developed a pharmacogenetic-based warfarin dosing algorithm specifically tailored for Brazilian individuals, a highly admixed population. It was shown to be more accurate than internationally developed algorithms for individuals from the Brazilian population [21]. Likewise, some other studies have shown that pharmacogenetic algorithms could be more accurate when developed and applied on specific populations [22–24].

Furthermore, studies showed the ability to improve TTR, compared with traditional anticoagulation, using strategies such as educational intervention, point-of-care testing, and the use of family practice clinics [25–27]. In this context, there is no data in the literature on the specific testing of a pharmacogenetic algorithm in patients with low TTR (<50%). In addition, cost-effectiveness evaluations for this approach are scarce and a positive finding for a pharmacogenetic approach could be very useful in a program of individualized anticoagulation therapy [28–30].

Thus, the aims of this study are: to evaluate the impact of a genetic-based, population-specific, algorithm, compared to traditional anticoagulation, in the time to achieve the therapeutic target and in the percentage of TTR at 4 and 12 weeks; and to assess the cost-effectiveness of genotype-guided warfarin dosing in a specific cohort of patients with low TTR (<50%) from a tertiary cardiovascular hospital.

## Methods

### Trial design

We will recruit 300 patients with low TTR (<50%) from the Heart Institute- Clinical Hospital-University of São Paulo Medical School (InCor- HCFMUSP).

The study protocol was approved by the Ethics Committee for Medical Research on Human Beings of the Clinical Hospital of the University of São Paulo Medical School (SDC 4033/14/013). Signed informed consent will be obtained from all participants.

Figure 1 shows the study design. Physicians will select the eligible patients according to the described criteria. At the first consultation, the pharmacist will explain the study and, if the patient accepts to participate, he or she will then sign the term. Patients will be randomized into two groups: TA group (traditional anticoagulation) and PA group (pharmacogenetic anticoagulation). Randomization will be considered protocol starting date. Pharmacists will apply questionnaires and collect blood samples for DNA extraction and measure creatinine, AST and ALT.

**Fig. 1 Fig1:**
[figure not shown]
Flowchart of the study design

For the TA group, the physician will adjust the dose according to the current INR value based on current guidelines [31, 32]. For the PA group, the dose will be prescribed based on data from each patient applied in a pharmacogenetic algorithm. In some cases, used algorithm may provide a counter-intuitive dose, i.e., a dose that is not adequate for adjusting the current patient’ INR (for example, a higher dose for a patient that already has a high INR). In these cases, the physician will adjust the dose following clinical criteria based on published guidelines and these patients will be kept on PA group [3, 33]. Patients of both groups will receive the medication and receive the pharmaceutical care. On the day after randomization, the pharmacist will inform, by phone, the new weekly dose prescribed for patients of both groups.

At the second (7 days), third (14 days), fourth (21 days), and fifth (28 days) consultations (with an interval of 7 days each), warfarin dosage will be adjusted, if necessary, based on current guidelines [31, 32].

After the fifth consultation, if the patient’s INR is within therapeutic target, the next measurement will be made after 30 days. If the patient’s INR is not in the therapeutic target, the warfarin dose adjustment will be made and the next INR measurement will be made after 7 days. The main outcomes will be the time to achieve the therapeutic target and the percentage of TTR at 4 and 12 weeks. We will measure the INR of all patients at the 12th week, independently of the value of INR before of this endpoint.

### Participants

Only patients with atrial fibrillation, above 18 years, and with TTR <50% based on the last three values of INR will be included in this study. Patients will be excluded if they have reached a stable dose of warfarin, liver dysfunction, alcoholism, use of another anticoagulant, use of chemotherapy, if they changed the dose of amiodarone 1 week before or if they do not meet the inclusion criteria.

### Interventions

For the TA group, the physician will adjust the dose according to the current INR value based on current guidelines [31, 32] and using an EP mobile tool for dividing the weekly dose in the days with the availability of tablets [34].

Patients with INR values <1.8 or >3.2 will undergo dose adjustment. For patients with an INR value from 1.8 to <2.0 or from >3.0 to 3.2, warfarin dose will be maintained and INR tests will continue to be made every 7 days. Then, if the patient continues to demonstrate values from 1.8 to <2.0 or from >3.0 to 3.2, warfarin dose will be changed. At each patient consultation, the pharmacist will check the drug adherence counting pills and adverse events using patient self-reporting information. The average weekly warfarin dose will be changed according to patient’s INR value: ≤1.5, increase by 20%; >1.5–<2.0, increase by 5%; >3.0–3.5, decrease by 5%; >3.5–<6.0, hold 1 dose, decrease by 15%; ≥6.0, hold warfarin and consider vitamin K based on guidelines [31, 32].

For the PA group, the dose will be prescribed based on data from each patient applied in a pharmacogenetic algorithm for the first consultation, after will adjust the dose based on guidelines and using the EP mobile [21].

### Outcomes

We will use the time to achieve the therapeutic target as primary outcomes measures and the TTR percentages as second outcome measures. We will consider that achieve the therapeutic target is three INR’s values within the therapeutic target. We will calculate the TTR in 4 and 12 weeks of follow-up.

### Sample size

With a sample size of 150 patients for each arm separately, the study will have a power of 80% to observe a difference of 8% between TTR means of the TA and PA groups, using sigma of 25% and alpha of 0.05.

### Randomization

Patients will be randomized into two groups: TA group (traditional anticoagulation) and PA group (pharmacogenetic anticoagulation). The randomization method will be by original generator, which allowed for only one block size. We will use the randomization.com to perform the randomization automatically [35]. We will add two arms with 150 subjects each. Afterward, we will include the list of randomization on the REDCap. This web application choose automatically the arm according to the list of randomization in a way that the information can not be change.

### Blinding

In this study, patients will be blinded and will not know their genetic results. The study team will not be blinded.

### Laboratorial measures and questionnaires

Oral anticoagulant therapy will be assessed by the prothrombin time (PT) in an automated coagulometric method. Venous blood samples will be collected in tubes containing sodium citrate 3.8%. INR calculation will be obtained by the ratio PT of the patient/normal PT controls, elevated to the international sensitivity index. Besides current INR, past INR values will be checked in electronic medical records. TTR will be calculated by the Rosendaal method [36], which uses linear interpolation to assign an INR value to each day between successive observed INR values. Peripheral venous blood will be collected into a BD Vacutainer System® without anticoagulant for measurements of serum creatinine, alanine aminotransferase (ALT), and aspartate aminotransferase (AST) by colorimetric and enzymatic assays.

Physicians and pharmacists will also complete a questionnaire for each patient. These will include the following variables: name, age, sex, body mass index, smoking, weekly intake of alcoholic beverages, weekly intake of dark green vegetables, comorbidities, results of last INR values, adverse events, and other drug use. In addition, the physician will evaluate the patients with the CHADS_2_VASC_2_ and HAS-BLED scores [37–39]. The CHADS_2_VASC_2_ score estimates stroke risk in patients with atrial fibrillation. The variables are congestive heart failure, hypertension, age ≥ 75, diabetes mellitus, a history of stroke or transient ischemic attack symptoms and vascular disease history [37, 38]. The HAS-BLED score estimates the risk of major bleeding for atrial fibrillation patients on anticoagulation care. “HAS-BLED” is an acronym for Hypertension (uncontrolled, systolic blood pressure >160 mmHg), Abnormal liver (cirrhosis or bilirubin >2x normal or AST/ALT/alkaline phosphatase >3x normal) and renal function (dialysis, transplant, creatinine > 2.6 mg/dL), Stroke history, Bleeding predisposition or Prior Major Bleeding, Labile INRs (unstable/high INRs or TTR < 60%), Elderly (age ≥ 65), Drugs (antiplatelet agents, nonsteroidal anti-inflammatory) or alcohol usage (≥8 drinks/week) [39]. Each patient will have an individual record, which remains with the group of pharmacists and physicians. This record will provide information on current warfarin dose (mg/week), daily dose, and INR values. Furthermore, each patient will have a card to register the warfarin daily dose.

The information gathered in the study will be managed using REDCap (Research Electronic Data Capture) tools hosted at the Clinical Hospital from the University of São Paulo Medical School. REDCap is a secure, web-based application designed to support data capture for research studies [40].

### Genotyping and predicted metabolic phenotypes

We will collect blood samples using the BD Vacutainer System® containing K_3_EDTA (Becton Dickinson, USA). We will use the QIAamp DNA Blood Kit (QIAGEN, Hilden, Germany) to extract genomic DNA from peripheral blood leukocytes. Genotyping of *CYP2C9*2* (c.430C > T, rs1799853), *CYP2C9*3* (c.1075A > C, rs1057910), and *VKORC1* 3673 (g.1639G > A, rs9923231) polymorphisms will be detected by real time PCR assays using Taqman probes (Applied Biosystems, CA, USA). We will use positive and negative reference samples to test along with the unknown samples in each run. TaqMan probe assay IDs: CYP2C9*2: C__25625805_10, CYP2C9*3: C___27104892_10, VKORC1 3673: C__30403261_20.

Patients will be divided into three distinct predicted phenotypes: extensive metabolizer (EM: wild-type genotypes for the *CYP2C9* polymorphisms - *1/*1), intermediate metabolizer (IM: heterozygous genotypes for the loss-of-function *CYP2C9* polymorphisms - *1/*2 or *1/*3) and poor metabolizer (PM: polymorphic homozygous or compound heterozygous genotypes for the loss-of-function *CYP2C9* polymorphisms - *2/*2 or *3/*3 or *2/*3) [41, 42].

### Pharmacogenetic algorithm

The pharmacogenetic algorithm used in this clinical study was developed and validated by our group using two independent patient cohorts. It includes the variables age, sex, weight, height, self-declared race, use of amiodarone, use of enzyme inducers, *VKORC1* genotypes, and predicted phenotypes according to *CYP2C9* polymorphisms [21].

### Pharmacoeconomic analysis

In these analyses we will evaluate the cost-effectiveness of both groups (TA and PA) calculating the costs of the genetic test, INR tests, and physician visits; and the effectiveness of the anticoagulation. We will also estimate costs that will be used to calculate the QALYs (quality-adjusted life year). These results that are used in QALYs are major bleeding, major thromboembolic events, and death. Major bleeding includes any episode of bleeding that requires hospitalization and thromboembolic events include embolic stroke, systemic embolism, ischemic attacks, deep venous thrombosis and pulmonary embolism.

### Statistical analysis

Statistical analyses will be carried out using SPSS software (v. 16.0, IBM, New York, NY) and the level of significance set at p ≤ 0.05. Pharmacoeconomic data will be evaluated using the TreeAge software (TreeAge, Inc., Williamstown, MA). Chi-square tests will be performed for comparative analysis of the categorical variables (such as adverse events, and evaluation of percentage of INR within therapeutic range) according to the polymorphisms or with the two approaches that will be made (TA and PA). Students’ *t*-tests or Mann-Whitney tests will be used for comparing TTR means and the time to achieve the therapeutic range according to the two groups. In addition, multivariate linear regression analysis will be used to identify variables associated with the TTR mean and with the time necessary to achieve the therapeutic range. A new randomization will not be performed for substitution of patients with missing data.

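### The chi-square test on the share of INRs in range has no stated unit; if INR measurements are counted, repeated INRs from one patient are treated as independent and the false-positive rate exceeds 5%

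*Protocol article*

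**What the plan says.** The Statistical analysis section of the protocol article sets a test for this measure: "Chi-square tests will be performed for comparative analysis of the categorical variables (such as adverse events, and evaluation of percentage of INR within therapeutic range"). The comparisons are made "according to the polymorphisms or with the two approaches that will be made (TA and PA"), with "the level of significance set at p ≤ 0.05". No visit, cut-off or count of patients is attached to the percentage. TTR and time to target are handled in a separate sentence, by t-test or Mann-Whitney.

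The Trial design section (text after Figure 1) fixes how many INRs each patient supplies. Visits in the first month are the same for all: "At the second (7 days), third (14 days), fourth (21 days), and fifth (28 days) consultations (with an interval of 7 days each"). After that the interval depends on the result: "if the patient’s INR is within therapeutic target, the next measurement will be made after 30 days", and otherwise after 7 days. Everyone has an INR at week 12.

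The Outcomes section declares time to target as primary and TTR at 4 and 12 weeks as secondary. The share of INRs in range is not declared as an outcome.

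**The concern.** A per-patient percentage is continuous and would belong with TTR in the t-test or Mann-Whitney sentence. The plan instead calls this measure categorical. The most direct way to make it so is to classify every INR as in or out of range and cross-tabulate by arm or genotype. A chi-square test then needs independent observations, and several INRs from one patient are not independent. The plan's own logic assumes that control is partly a patient trait: entry depends on a patient's last three INRs, and regression is planned to find patient variables associated with TTR.

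A second, separate issue follows from the visit rule. After day 28, a poorly controlled patient adds more INRs to a pooled count than a well controlled one.

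At stake is a spuriously significant difference in anticoagulation quality, between arms or genotypes, reported beside the TTR result.

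**Working it through.** **The plan's own figure.** The Sample size section claims 80% power for "a difference of 8% between TTR means of the TA and PA groups, using sigma of 25% and alpha of 0.05". With 150 per arm, SE = 25 × √(2/150) = 2.887, 8/2.887 = 2.771, and Φ(2.771 − 1.960) = 79.1%. Exact 80% needs 154 per arm. The figure is reproduced for a two-sided test. It concerns mean TTR; the document gives no error rate or correlation for the chi-square test.

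**INRs per patient (Trial design).**
- By week 4: days 7, 14, 21, 28, so m = 4 for everyone.
- By week 12, always in range: days 7, 14, 21, 28, 58, 84, so m = 6.
- By week 12, always out of range: weekly to day 84, so m = 12.
- Simulated mean on this schedule: about 7.7.

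**Formula if INRs are pooled.** Design effect D = 1 + (m − 1) × ICC; true alpha = 2 × [1 − Φ(1.96/√D)]. The ICC is assumed. Example: m = 4, ICC 0.20 gives D = 1.60, 1.96/√1.60 = 1.55, alpha = 12.1%.

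**Simulation.** 3,000 null trials per ICC, 150 per arm, with a constant in-range probability for each patient (beta-distributed, mean 50%) and the 12-week visit rule.

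| ICC | Formula, m = 4 (week 4) | Formula, m = 6 | Formula, m = 8 | Formula, m = 12 | Simulated, week 12 | Pooled % in range (true 50%) |
|---|---|---|---|---|---|---|
| 0.05 | 6.8% | 8.0% | 9.2% | 11.5% | 9.5% | 49.2% |
| 0.10 | 8.6% | 11.0% | 13.3% | 17.6% | 11.9% | 48.4% |
| 0.15 | 10.4% | 13.8% | 17.1% | 22.9% | 17.7% | 47.6% |
| 0.20 | 12.1% | 16.6% | 20.6% | 27.3% | 22.7% | 46.8% |

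A separate run of 1,000 null trials per ICC gave 9.8%, 13.7% and 21.9% at ICC 0.05, 0.10 and 0.20. With ICC 0 the simulated rate is 5.5%.

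**Is this ICC range reasonable?** As a rough guide, treat the 25-point SD as the SD of a per-patient proportion with p = 0.5 and m = 8. Then 0.0625/0.25 = 0.25, ICC = (0.25 − 1/8)/(1 − 1/8) = 0.143, D = 8 × 0.25 = 2.0, and alpha = 16.6%. Independent INRs would give an SD of only √(0.25/8) = 17.7 points. This is indirect, because the stated SD is for interpolated TTR.

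**Weighting.** The last column falls short of 50% by 0.8, 1.6, 2.4 and 3.2 points. Averaging each patient's percentage over all of that patient's INRs does not fully repair this: at ICC 0.15 it gives 51.7%, 1.7 points too high, because the number of INRs still depends on the results. Using only the visits common to everyone removes that dependence.

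**Is weighting the source of the false positives?** No. At week 4 every patient has four INRs, so nobody is over-weighted, yet alpha is already 6.8% to 12.1%. Both arms also follow the same visit rule, so under the null the shift is the same in each.

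**One value per patient.** In the simulations a t-type test on per-patient percentages rejected in 4.2% to 5.6% of null trials, and chi-square on the single week-12 INR in 5.3% to 6.1%. Both are about nominal.

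**The case against.** The strongest reply is that the plan never says INRs are pooled. The measure could be a patient-level category, such as in range or not at week 12, or above or below a TTR cut-point like the 50% and 65% values in the Background. Adverse events, named in the same parenthesis, can naturally be counted per patient. For a patient-level category chi-square is valid. The article is also a condensed text, and the unit of a supportive comparison may be defined in an analysis plan that is not shown.

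The first part stands in that a reader might infer that the protocol prescribes a pooled test, and its wording does not go that far. But the patient-level reading requires a visit or cut-off that the sentence lacks, while the literal denominator is INRs. On the second part, the point does not rest on an omitted detail: the article itself chooses the test and labels the variable categorical.

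A reader might also take a fixed multiplier, such as two to four times nominal, as established. The documents give no ICC. At m = 8 that multiplier needs an ICC of about 0.06 to 0.19. Over ICC 0.02 to 0.30 and m = 6 to 12, alpha runs from 6.2% to 34.5%, about 1.2 to 7 times nominal. At week 4, with ICC 0.05 to 0.20, it is only 1.4 to 2.4 times.

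The objection that impact is limited also stands: TTR and time to target are compared with one value per patient.

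**Conclusion.** The point holds conditionally. The plan assigns chi-square to the share of INRs in range without stating the unit. If INR measurements are counted, which is the literal though not the only reading, the false-positive rate is about 7% to 12% at week 4 and about 10% to 22% at week 12. These figures assume an ICC of 0.05 to 0.20, a two-sided 5% level and, in the simulation, an in-range probability that is constant over time for each patient. The simulation covers the comparison of arms; the genotype comparison shares the clustering problem, but its size was not simulated.

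The over-weighting of poorly controlled patients is a distinct matter of what is estimated. It applies only to a pooled count that runs past day 28, and amounts to roughly 1 to 3 points over the same ICC range. The documents do not support the inference that it drives the false positives, nor that the primary or secondary results are compromised.

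**What to change.** In the Statistical analysis section, take the share of INRs in range off the chi-square list. Compute one percentage per patient from the INRs scheduled for everyone (days 7, 14, 21, 28 and week 12) and compare it with the same patient-level test as TTR. Alternatively, model in-range status at those visits by logistic GEE clustered on patient. Keep chi-square for variables with one value per patient, such as any adverse event. If a patient-level category was meant all along, chi-square can stay, with the visit or cut-off written into the sentence.

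The cost is a change of analysis wording. No visit, measurement or sample size changes. Compared with a pooled test, the p-value on this supportive measure will usually be less favourable, and the extra INRs taken between day 28 and week 12 are not used for it.

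### The primary outcome is a time to event cut off at about week 12, but its named tests are for fully observed times and make no provision for patients not at target by then

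*Protocol article*

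**What the plan says.** The Outcomes section of the protocol article sets the order of outcomes: "We will use the time to achieve the therapeutic target as primary outcomes measures and the TTR percentages as second outcome measures". It defines the event: "achieve the therapeutic target is three INR’s values within the therapeutic target". It does not say whether the three values must be consecutive.

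The Trial design section (text after Fig. 1) sets the measurement times. INRs are taken "At the second (7 days), third (14 days), fourth (21 days), and fifth (28 days) consultations". After day 28, "if the patient’s INR is within therapeutic target, the next measurement will be made after 30 days"; otherwise the next INR is 7 days later. A closing measurement is compulsory: "We will measure the INR of all patients at the 12th week, independently of the value of INR before of this endpoint".

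The Statistical analysis section offers Student's t-tests or, in its words, "Mann-Whitney tests will be used for comparing TTR means and the time to achieve the therapeutic range according to the two groups". It adds that "multivariate linear regression analysis will be used to identify variables associated with the TTR mean and with the time necessary to achieve the therapeutic range". Its only sentence on missing data is that patients will not be replaced by a new randomisation. No survival method is named, and no time, rank or censoring rule is given for a patient who has not reached target.

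**The concern.** Patients enter because their control is poor (TTR below 50% on the last three INRs), so some will probably not have three in-target INRs by week 12. For them the time is known only to exceed the follow-up. A t-test or a linear regression needs a number for each patient, and a Mann-Whitney test needs at least a rank. The analyst must therefore drop these patients, enter a value, or assign a rank, and the plan does not say which.

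Dropping them compares reachers with reachers. Those groups are formed after randomisation and may differ if treatment changes who reaches target. The comparison also discards any difference in the proportion reaching target, which is a large part of what a better starting dose could achieve. The study team is not blinded (Blinding section), so a choice made after the data are seen would leave the primary result open to question.

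**Working it through.** **1. The plan's own figure.** The Sample size section gives 80% power with 150 per arm for an 8-point TTR difference, SD 25, alpha 0.05 (two-sided assumed).
- n per arm = 2(1.96 + 0.8416)² × 25² / 8² = 153.3, so 154.
- Power at 150 = Φ(8 / (25√(2/150)) − 1.96) = Φ(2.771 − 1.96) = 0.79.

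The figure reproduces. It concerns TTR, the secondary outcome, so the article states no power for time to target.

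**2. Are unobserved times possible under the schedule?** Count follow-up INRs only, on the scheduled days, with week 12 as day 84.
- First in range on day 28: next INR on day 58, then day 84 (58 + 30 = 88 is later). The third in-range value comes on day 84 at the earliest.
- First in range on day 49: next on day 79, then day 84. Again day 84 at the earliest.
- First in range on day 56: 56 + 30 = 86, so only the day-84 INR remains. Two values at most.

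A patient first in range on day 56 or later therefore cannot reach target by week 12. Patients first in range on days 28 to 49 can reach it only at day 84.

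**3. Size under the schedule.** Assumptions, none of them from the article: in-range probability per INR of 0.40 to 0.60 in TA and 8 points higher in PA; variation between patients by a beta distribution with concentration 5 or 20; 150 per arm; two-sided 0.05; 300 simulated trials per scenario. The simulation error of a power near 0.5 is √(0.25/300) = 0.03.

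| Event | TA / PA in range | Conc. | Reached TA / PA | Log-rank | Mann-Whitney, reachers | Mann-Whitney, non-reachers last | t-test, capped at day 84 |
|---|---|---|---|---|---|---|---|
| Any three | 0.40 / 0.48 | 5 | 0.64 / 0.75 | 0.68 | 0.22 | 0.70 | 0.63 |
| Any three | 0.50 / 0.58 | 5 | 0.77 / 0.85 | 0.64 | 0.28 | 0.64 | 0.59 |
| Any three | 0.60 / 0.68 | 20 | 0.94 / 0.97 | 0.75 | 0.62 | 0.75 | 0.75 |
| Consecutive | 0.40 / 0.48 | 20 | 0.27 / 0.38 | 0.54 | 0.07 | 0.55 | 0.40 |
| Consecutive | 0.50 / 0.58 | 5 | 0.43 / 0.54 | 0.47 | 0.08 | 0.46 | 0.38 |
| Consecutive | 0.60 / 0.68 | 20 | 0.57 / 0.70 | 0.71 | 0.19 | 0.72 | 0.65 |

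Ranges over all scenarios run:
- Any three: 6-36% of TA not at target; log-rank 0.60-0.80; Mann-Whitney among reachers 0.22-0.62.
- Consecutive: 43-73% of TA not at target; log-rank 0.47-0.71; Mann-Whitney among reachers 0.05-0.19.

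**4. Attenuation.** Share lost = 1 − (mean difference among reachers) / (mean difference with time capped at day 84).
- Any three, 0.40 / 0.48, concentration 5: 1 − (48.55 − 44.86)/(61.47 − 54.60) = 1 − 3.69/6.87 = 46%.
- Any three, 0.60 / 0.68, concentration 20: 1 − 5.06/6.43 = 21%.
- Consecutive, 0.50 / 0.58, concentration 5: 1 − 1.91/5.15 = 63%.
- Consecutive, 0.60 / 0.68, concentration 20: 1 − 3.70/7.38 = 50%.

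**5. Check with a second model.** Exponential times with TA hazard −ln(s)/84, where s is the share of TA not at target by day 84; assumed hazard ratio 1.4; 500 runs.

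| s | Log-rank | Mann-Whitney, reachers | Mann-Whitney, non-reachers last | t-test, capped |
|---|---|---|---|---|
| 10% | 0.80 | 0.45 | 0.71 | 0.79 |
| 30% | 0.72 | 0.18 | 0.69 | 0.70 |
| 50% | 0.58 | 0.06 | 0.54 | 0.51 |

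At s = 30% there were 226.9 events on average. Schoenfeld's formula gives Φ(√(226.9/4) × ln 1.4 − 1.96) = Φ(2.53 − 1.96) = 0.72, in agreement with the simulation.

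**The case against.** The strongest reply is that the named tests can be made to work. With a common cut-off, Mann-Whitney can place all non-reachers last; its power is then within about 4 points of log-rank under the visit schedule and at most about 9 points lower in the exponential model. A t-test on times capped at day 84 compares restricted mean times, a recognised quantity. So a reader who infers that these methods cannot use non-reachers goes too far. This part of the reply stands. However, the article states neither rule, and both misstate a patient lost at, say, week 3, who would be scored as a failure or as 84 days. Capping also gives a patient who reaches target on day 84 the same value as one who never does; under the visit schedule it cost up to 16 points against log-rank (0.62 against 0.46).

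Three other stronger readings are tempting and are not supported:
- **That most of the treatment effect is lost.** This requires non-reachers to be excluded, which the article does not say. Even then, with any three INRs the loss under the visit schedule is 21-46%, which is less than half.
- **That many patients will certainly fail to reach target.** The schedule makes unobserved times possible, but the article gives no rate.
- **That exclusion would manufacture a benefit.** With no effect of treatment, reachers in the two arms have the same distribution, so exclusion alone does not create a false positive. The harm is attenuation and lost power.

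Two smaller points are fair. No sentence says when observation of time to target stops; week 12 is the natural reading of the compulsory final INR. And a condensed article may leave scoring rules to a fuller document. But the choice of tests and of linear regression is stated here, and that choice does not suit censored times.

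**Conclusion.** The concern holds in a limited form. The stated methods for the primary outcome are methods for fully observed times, applied to a time that the protocol's own visit schedule can leave unobserved, with no rule for non-reachers or early dropouts. If non-reachers are dropped, power falls from 0.60-0.80 to 0.22-0.62 when any three INRs count, and from 0.47-0.71 to 0.05-0.19 when they must be consecutive. The loss is smallest when nearly everyone reaches target: 0.75 to 0.62 with 6% of TA not reaching.

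The direction does not depend on the model, but the size does. It rests on assumed in-range probabilities, an assumed 8-point difference, a week-12 cut-off and a definition of the event that the article leaves open. If a worst-rank or capping rule were in fact applied, the remaining fault would be mainly the handling of early dropout, the linear regression on time, and some loss of power from capping.

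**What to change.** In the Statistical analysis section, analyse time to target from randomisation in all randomised patients with Kaplan-Meier curves and a log-rank test, censoring at the last INR (week 12 for completers). This assumes that dropout is unrelated to the chance of reaching target, and the text should say so. Replace linear regression on time with a Cox model with a stated method for ties, or a discrete-time model, since times fall on scheduled visit days and many can fall on day 84. Keep the t-test or linear model for TTR.

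At minimum, if Mann-Whitney is kept, fix in advance that non-reachers rank behind every reacher, including those who reach target on day 84, and say how early dropouts are scored.

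In the Outcomes section, state whether the three INRs must be consecutive and that observation ends at week 12.

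The cost is about a paragraph of text. No new data, visits or patients are needed.
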